## 8.3 Concomitant Therapy

Participants will be directed to contact their GP for hearing aid referral to a rapid access service such as is provided by accredited ‘Any Qualified Provider’ (AQP) high street audiologists. Any form of hearing aid provision including tinnitus maskers will be permitted and this will be recorded via participant questionnaire.

No medication is administered within the study, nor are any medications prohibited.

## 8.4 Adherence

The number of participants continuing with the intervention at 3 and 6 months will be assessed, as a measure of adherence to the Oto Programme.

# 9. SAFETY REPORTING

## 9.1 Definitions

| Adverse Event (AE) | Any untoward medical occurrence in a participant to whom a medicinal product has been administered, including occurrences which are not necessarily caused by or related to that product. |
| --- | --- |
| Serious Adverse Event (SAE) | A serious adverse event is any untoward medical occurrence that:   - results in death - is life-threatening - requires inpatient hospitalisation or prolongation of existing hospitalisation - results in persistent or significant disability/incapacity - consists of a congenital anomaly or birth defect*.   Other ‘important medical events’ may also be considered a serious adverse event when, based upon appropriate medical judgement, the event may jeopardise the participant and may require medical or surgical intervention to prevent one of the outcomes listed above.  NOTE: The term "life-threatening" in the definition of "serious" refers to an event in which the participant was at risk of death at the time of the event; it does not refer to an event which hypothetically might have caused death if it were more severe.  *NOTE: Pregnancy is not, in itself an SAE. In the event that a participant or his/her partner becomes pregnant whilst taking part in a clinical trial or during a stage where the foetus could have been exposed to the medicinal product (in the case of the active substance or one of its metabolites having a long half-life) the pregnancy should be followed up by the investigator until delivery for congenital abnormality or birth defect, at which point it would fall within the definition of “serious”. |

NB: to avoid confusion or misunderstanding of the difference between the terms “serious” and “severe”, the following note of clarification is provided: “Severe” is often used to describe intensity of a specific event, which may be of relatively minor medical significance. “Seriousness” is the regulatory definition supplied above.

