# 4 OBJECTIVES AND OUTCOME MEASURES

4.1 Randomised Controlled Trial

Primary Objective

| **Objective** | **Outcome Measure** | **Timepoint(s) of evaluation** |
| --- | --- | --- |
| Assess whether Oto’s digital tinnitus programme is as effective at reducing self-reported tinnitus severity as therapist- delivered CBT | Total TFI score | Primary outcome is total TFI score at 6 months  TFI evaluated at:  Baseline, 1, 3, 6 and 12 months |

Secondary Objectives

| Objective | Outcome Measure | Timepoint(s) of evaluation |
| --- | --- | --- |
| Assess whether Oto’s digital tinnitus programme is superior to therapist-delivered CBT in reducing self-reported tinnitus severity | Total TFI score | Total TFI score at 6 months |
| Assess the self-reported impact of Oto’s digital tinnitus programme on aspects of participants tinnitus experience | 8 Tinnitus Functional Index subscales (Intrusive, Sense of Control, Cognitive, Sleep, Auditory, Relaxation, Quality of Life and Emotional). | Baseline, 1, 3, 6 and 12 months |
| Assess the impact on overall health-related quality of life of Oto’s digital programme and therapist delivered tinnitus therapy | EuroQol EQ-5D-5L and Health Utilities Index Mark 3 (HUI3) | Baseline, 3, 6 and 12 months |
| Assess the usability of the Oto digital programme | System Usability Scale | 3 months |
| Explore participants views of the impact and usability of the two interventions | Thematic analysis of focus groups and semi structured interviews | 3, 6 and 12 months |
| Understand the health economics of the two for tinnitus | Cost-utility analysis | Over trial period covering from baseline to 12 months |
| Assess the number of adverse events between the groups | eCRF | Randomisation to 3 months |
| Assess intervention Adherence | Number of participants completing the intervention | Number of participants starting the intervention at baseline compared to those completing the intervention at 3 and 6 months |

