## 7.8 Administration of intervention

Following baseline data collection the participant will be granted access to either the trial intervention or control intervention. Access to the Oto app will be immediate. The first face-to-face CBT appointment will be scheduled within +/- 1 week.

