## 8.2 Control Group

Those allocated to the control arm of the study will undertake one to one tinnitus tinnitus therapy from a trained Audiologist/Hearing Therapist/Psychologist via video calls. This is not a direct mirror of NHS practice as patients will have rapid access to therapy, rather than typical long waiting times from GP referral. Participants in the control group will agree to not use Oto or an alternative tinnitus app for the duration of the study.

This control intervention will consist of a minimum of 1 tinnitus therapy session, with further sessions at the discretion of the participant and therapist up to a maximum of 6. Therapy will begin within 1 week of randomisation. There will be a panel of therapists selected to deliver the therapy. The therapy will include several elements of current standard care formulated into a personal management plan. :

- Assessment of participant needs
- Participant education
- CBT
- Relaxation therapy
- Signposting to hearing aid fitting and other support

In order to facilitate retention, participants in the control group will be offered the Oto Tinnitus Programme at the end of the 12-month RCT period.

Therapists will provide data to Lindus Health on attendance and number of sessions for each participant.

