## 9.3 Adverse Event Reporting

We do not anticipate that the study intervention (Oto Digital Tinnitus Programme) should result in any adverse events (AEs) but include this section in case such events are reported so that they can be considered for causal links to the study. Only AEs that are clinically judged by the research site PI (a medical Doctor at Lindus Health) as being caused by the trial intervention will be reported to the REC that gave favourable opinion. Participants will be asked in their follow up if they have experienced any side effects or medical events while participating in the DEFINE trial. Participants may also report potential (S)AEs via telephone calls or email correspondence with the central trial team. AEs will be collected from randomisation until and including the 3 month follow-up contact.

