- Discussion/ documentation of progress and outcome of treatment plan
- Onward referral if appropriate
- Further follow-ups can be arranged as required and according to departmental policy.

At any stage in the intervention the therapist may consider onward referral if appropriate and after discussion with the participant

This could include the following:

- Audiology: hearing aid assessment and fitting, ear level sound generator fitting/ combi device fitting or further diagnostic tests
- GP: to request counselling or a formal psychological or psychiatric referral; medication review

o Where a patient has significant anxiety or depression and is judged to be at significant risk of self-harm, the GP should be contacted immediately by phone. The patient should be made aware of this and encouraged to see their GP urgently.

o If a patient has significant anxiety and depression but is not suicidal, then discuss a local referral with their GP, or self-refer for psychology support via Improving Access to Psychological Therapies.

- ENT: further tinnitus investigations, vestibular assessment
- Physiotherapy: relaxation exercises.

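### The adverse event definition is medicinal-product wording that fits neither arm, and relatedness is framed around the Oto programme, leaving events caused by the control therapy without a clear route to be classed or reported as related

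*Protocol*

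**What the plan says.** The AE definition in protocol section 9.1 begins "Any untoward medical occurrence in a participant to whom a medicinal product has been administered". The pregnancy note in the same table also speaks of exposure to a medicinal product and its metabolites. The SAE definition beside it has no such condition: "A serious adverse event is any untoward medical occurrence that", followed by the usual seriousness criteria. Section 8.3 states: "No medication is administered within the study, nor are any medications prohibited".

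On causality, section 9.2 requires each event to be judged against the intervention and does not say which arm's treatment that is. Section 9.3 names the Oto programme in brackets as the study intervention. It restricts AE reporting to the REC to events judged "as being caused by the trial intervention will be reported to the REC that gave favourable opinion". Section 9.5 lists fluctuation in tinnitus severity and related mood as expected. Such events become SAEs only if felt to be directly related to the study intervention or to the qualitative work.

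Section 7.8 separates the two treatments by name: after baseline the "participant will be granted access to either the trial intervention or control intervention". Section 4.1 sets the secondary objective: "Assess the number of adverse events between the groups", from randomisation to 3 months.

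**The concern.** There are two linked faults. First, the definition that should say what counts as an AE depends on exposure that the study does not provide in either arm. Staff must set the written definition aside to carry out the collection that section 9.3 describes.

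Second, where causality decides what happens to an event, the text names only one arm's treatment. The control is an active psychological therapy delivered by the trial, in people whose condition can be distressing. A deterioration in mood during treatment is a plausible event in either arm. If it is attributed to the app, sections 9.3 and 9.5 provide a path. If it is attributed to a therapist session, the path is unclear. At stake are the related/unrelated split by arm, the SAE listing for the tinnitus and mood events in 9.5, and what the REC sees. Any safety statement comparing the app with therapist care would draw on these.

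**Working it through.** No arithmetic applies, because the protocol gives no expected AE rate and no figure for this outcome. The check sets the passages side by side.

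1. **Definition against treatment given.** Section 9.1 requires that a medicinal product has been administered. Section 8.3 says the study administers none. So neither study treatment, app or therapist sessions, can bring an event within the definition. At most the wording reaches participants who take medicines of their own, which is unrelated to either allocated treatment.

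2. **Definition against collection.** Section 9.3 has participants asked at follow-up about side effects and medical events, with no condition on arm or medication. Sections 7.10.1 and 7.10.2 list AEs at months 1 and 3, and the schedule in Appendix 2 has one AE review row for all participants. Collection is therefore wider than the definition, and the two do not agree.

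3. **SAE route.** The SAE definition is free of the medicinal-product condition, but section 9.4 starts from AEs that meet the SAE criteria. Taken strictly, the defect in 9.1 passes to the SAE route.

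4. **What the intervention means.**
   - Section 9.2: the intervention, arm not stated.
   - Section 9.3: the study intervention is Oto; REC reporting of AEs depends on the trial intervention.
   - Section 7.8: trial intervention and control intervention are alternatives.
   - Section 9.5: expectations for SAEs name the digital intervention, data collection and focus groups; the control therapy is not named.
   - Section 12.5: trial interventions, in the plural, covers both arms.
   - Section 8.2 and Appendix 3: the control therapy is itself called an intervention.

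   Usage is inconsistent, but the two passages where causality triggers an action (the AE reporting rule in 9.3 and the SAE rule in 9.5) lean towards Oto. No passage expressly requires relatedness to be judged against the control therapy.

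5. **Same event, two arms.** Suppose a worsening of mood related to tinnitus meets a seriousness criterion. If it is judged to be caused by the app, 9.5 lets it be an SAE and 9.4 then applies. If it is judged to be caused by a therapist session, the exception in 9.5 does not clearly cover it. It may therefore stay outside SAE classification, and 9.3 gives no clear basis for reporting it to the REC as a related AE.

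6. **Effect on the stated outcome.** The objective in 4.1 and the outcome in the synopsis count AEs whatever their relatedness. Steps 4 and 5 therefore bear on classification and reporting, not on the total count.

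7. **Scope.** 196 participants at 1:1 gives 196 / 2 = 98 in the control arm. This is the number of people for whom the route is unclear. It is not an estimate of events missed.

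**The case against.** The strongest reply is that this is leftover drug-trial wording with little practical effect. Section 9.3 and the schedule collect events from everyone. Section 9.2 asks for a causality judgement on each event and does not limit it to Oto. Section 9.4 sends related and unexpected SAEs to the REC, and all SAEs to the sponsor, without distinction of arm. Section 9.6.1 gives both arms a distress call four weeks after randomisation and central monitoring of Tinnitus Functional Index (TFI) scores.

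Much of this stands, and it rules out several stronger readings that a reader might infer:

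- *That the AE outcome is empty by definition.* This follows only from the 9.1 sentence read alone and confined to study-administered products. Collection covers all participants, and people on their own medicines meet even the literal wording.
- *That the between-arm count is biased by the causality wording.* The count does not depend on relatedness.
- *That a control participant can never have a related event.* Section 9.2 is ambiguous, not exclusive.
- *That therapist contacts give the trial no safety information.* Section 8.2 says "Therapists will provide data to Lindus Health on attendance and number of sessions for each participant", but does not say that they return nothing else. Appendix 3 provides that where a patient with significant anxiety or depression "is judged to be at significant risk of self-harm, the GP should be contacted immediately by phone", and the protocol states no route from there to the AE record. That route is operational detail which may sit elsewhere, and control participants still report through the common follow-up. Adding therapist-sourced events could also make ascertainment unequal between arms.

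The reply does not remove the conflict between 9.1 and sections 8.3 and 9.3. Nor does 9.4 rescue the second fault: it acts only on events already classed as SAEs, and its REC route also requires them to be related. Those are the classifications that 9.5 and 9.2 leave unclear for the control arm.

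**Conclusion.** The point holds as a wording defect with consequences for safety classification. The AE definition in 9.1 fits neither arm and must be reconciled with 8.3 and 9.3. Sections 9.3 and 9.5 frame causality around Oto, so harm from the control therapy has no clear route to be classed as related, to be an SAE under 9.5, or to be reported to the REC as a related AE.

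The second part assumes that the study and trial intervention in 9.3 and 9.5 carry the meaning given by the bracket in 9.3 and the contrast in 7.8. The looser usage in 12.5 and Appendix 3 makes this a strong inference, not a certainty. The size is qualitative: it concerns the related/unrelated and SAE listings and the REC reports for the control half of the trial, while the total AE count by group remains usable. The protocol should be corrected, but the planned between-arm count is not invalidated.

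**What to change.** In 9.1, define an AE as any untoward medical occurrence in a randomised participant, in either arm, whether or not related to the allocated treatment. Remove the medicinal-product wording there and in the pregnancy note.

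In 9.2 to 9.5, state that relatedness is judged against the allocated treatment (the Oto programme or the therapist-delivered therapy), with the same causality categories and the same reporting rules in both arms. In particular, replace the references to the study and trial intervention in 9.3 and 9.5 with the allocated treatment, keeping the existing mention of the qualitative work in 9.5.

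The cost is a text amendment and slightly more events to assess and report. Collection, visit schedule and sample size are unchanged.

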## 9.2 Causality

The relationship of each adverse event to the intervention must be determined by a medically qualified individual according to the following definitions:

- **Unrelated** – where an event is not considered to be related to the intervention
- **Possibly** – although a relationship to the intervention cannot be completely ruled out, the nature of the event, the underlying disease, concomitant medication or temporal relationship make other explanations possible
- **Probably** – the temporal relationship and absence of a more likely explanation suggest the event could be related to the intervention.
- **Definitely** – the known effects of the intervention, its therapeutics class or based on challenge testing suggest that the intervention is the most likely cause.

All AEs (SAEs) labelled possibly, probably or definitely will be considered as related to the intervention.

## 9.3 Adverse Event Reporting

We do not anticipate that the study intervention (Oto Digital Tinnitus Programme) should result in any adverse events (AEs) but include this section in case such events are reported so that they can be considered for causal links to the study. Only AEs that are clinically judged by the research site PI (a medical Doctor at Lindus Health) as being caused by the trial intervention will be reported to the REC that gave favourable opinion. Participants will be asked in their follow up if they have experienced any side effects or medical events while participating in the DEFINE trial. Participants may also report potential (S)AEs via telephone calls or email correspondence with the central trial team. AEs will be collected from randomisation until and including the 3 month follow-up contact.

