| Primary Outcome | Total TFI score (Score of 0-250 with high score indicating worse outcome) 6 months from starting therapy |
| Secondary Outcomes | 1) Total TFI and TFI subscale scores at 1, 3 and 12 months  2) Participant health-related quality of life measured using the EuroQol EQ-5D-5L and the Health Utilities Index Mark 3 (HUI3) responses and summary scores at 3, 6 and 12 months follow-up from starting therapy  3) Adverse events from randomisation to 3 months  4) System Usability Scale scores at 3 months  5) Qualitative feedback from focus groups and semi structured interviews at 3, 6 and 12 months  6) Cost-utility analysis synthesising costs and QALYs over trial period  7) Assess intervention adherence at 3 and 6 months |
| Number of participants | 196 participants, randomised in a 1:1 ratio |
| Eligibility criteria | Inclusion Criteria   1. Aged 18 years or over 2. Experienced tinnitus symptoms for at least 3 months and self-assessed as having a significant impact on quality of life. 3. Have access to a smartphone 4. Able and willing to give consent for the study prior to participation 5. Able to speak and read English to a sufficient level.   Exclusion Criteria   1. Tinnitus with potential “red flag” symptoms i.e. unilateral or pulsatile tinnitus (assessed via a red flag checklist during the screening call) 2. Significant mental health problems e.g. history of suicidal ideation or requirement for psychiatric/psychological support beyond Primary Care level 3. Have required hospitalisation for depression or taking antipsychotic drug 4. Currently taking part in another clinical trial for hearing/tinnitus 5. Awaiting surgical intervention for hearing/tinnitus 6. Previously undergone tinnitus therapy of any type e.g. CBT or TRT 7. Pregnant and breastfeeding women   Additional Note: Patients with hearing aids are eligible to participate in the study |
| Intervention | The Oto digital programme for tinnitus. This involves direct access to a digital multi-modal therapy package incorporating CBT, physical therapy, mindfulness and relaxation therapy. |
| Comparator | Current standard of care (1-1 therapist-delivered CBT). |
| Duration of study | 18 months |
| Randomisation / Blinding | Randomised 1:1 by computer algorithm and stratified by age, sex and level of hearing loss. Unblinded. |
| Statistical analysis | Non-inferiority |
| Intervention Adherence | Number of participants in each group completing therapy programme by 3 months |

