### 7.10.2 Month 3 (Study week 12 +/- 14 days)

To collect data to include but not limited to:

- Complete TFI questionnaire
- Complete EQ-5D-5L and HUI3 questionnaires
- Adverse events
- Complete System Usability Score (SUS)
- Complete questionnaire on primary and community healthcare appointments and A&E visits related to tinnitus since week 4
- Complete questionnaire on personal out-of-pocket tinnitus related costs, any time-off work and travel information to appointments incurred since week 4
- Any change in medication (particularly medications known to be associated with tinnitus, e.g. Aspirin, diuretics) or introduction of hearing aid

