## 9.4 SAE Reporting

Any AEs which fall under the definition of a SAE will be reported to the Chief Investigator or designated person within 24 hours, to be reviewed for relatedness and expectedness. However, hospitalisations for elective treatment of a pre-existing condition do not need reporting as SAEs.

Reports of related and unexpected SAEs (in the opinion of the Chief Investigator or designated person) will be reported to the REC within 15 days of the CI and/or central trial team becoming aware of the event. The Chief Investigator will also notify the Sponsor of all study SAEs.

Any pregnancy occurring during the study will result in the immediate discontinuation of the participant and the Sponsor should be notified within 24 hours so appropriate follow-up is conducted. Pregnancy itself is not an AE.

All SAEs will be recorded in the Citrus platform and any concerns raised immediately with the CI and may be tabled for discussion at the regular Trial Management Group meeting or referred to an independent Trial Steering Committee (TSC) for review.

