## 9.6 Measures to minimise the occurrence of AEs

### 9.6.1 Tinnitus Distress Monitoring

Participants will self-monitor their tinnitus related distress via the TFI at follow up intervals. Throughout the trial they will be asked to use the traffic light system (see Appendix 4) to ensure that they seek medical care as required. To further prevent any potential safety events, the central Lindus Health team will also monitor TFI scores at follow up visits and using the traffic light system (see Appendix 3), alert the participant and their GP to any TFI measurements which require follow-up (this is defined as any TFI score of 180 or above). All participants will also receive a phone call from a member of the clinical central trial team, 4 weeks after randomisation, to answer any queries and to specifically identify any potential issues relating to psychological distress.

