## 17.6 Expenses and Benefits

Participants in the smartphone app delivered arm will receive free access to the intervention for the 12 months of the study. Those in the control group will receive a free subscription to the Oto tinnitus programme at the end of the 12 month trial period.

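### Planned AE review ends at month 3, leaving about three quarters of follow-up without it, and the protocol does not settle whether a later SAE is recorded

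*Protocol*

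**What the plan says.** **AE window.** Section 9.3: "AEs will be collected from randomisation until and including the 3 month follow-up contact". The synopsis lists the secondary outcome as "Adverse events from randomisation to 3 months", and the objectives table in 4.1 gives "Randomisation to 3 months". Appendix 2 ticks AE review at baseline, month 1 and month 3 and leaves months 6 and 12 blank. The visit lists in 7.10.3 and 7.10.4 contain no AE item.

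**SAEs.** Section 9.4 starts from AEs that meet the SAE definition. It then says "All SAEs will be recorded in the Citrus platform" and has the Chief Investigator notify the sponsor of every study SAE. It gives no end date.

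**What continues after month 3.**
- Section 5.2 assigns participants to their arm for 12 months. Section 17.6 says app-arm participants "will receive free access to the intervention for the 12 months of the study".
- Section 8.1 expects the app programme to be finished in about six weeks, but users may add further modules.
- Section 8.4 counts those still using the intervention at 3 and 6 months. Appendix 2 collects adherence data at months 6 and 12.
- Section 8.2 allows one to six control sessions, starting within a week of randomisation, with no stated end.
- Section 12.1 places focus groups at about 3, 6 and 12 months. Section 9.5 makes events directly related to the qualitative work an exception to its rule against reporting expected events as SAEs.
- Section 9.6.1 has the central team check TFI scores at follow-up visits and send an alert at 180 or above. TFI is collected at months 6 and 12.

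**Related wording.** The AE definition in 9.1 is limited to an occurrence "in a participant to whom a medicinal product has been administered", whereas 8.3 says the study administers no medication. Section 9.6.1 says: "Throughout the trial they will be asked to use the traffic light system (see Appendix 4". For the central team's use of the same tool, that section cites Appendix 3.

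**The concern.** Comparing the number of AEs between arms is a stated secondary objective, and section 9.5 names psychological deterioration as the event participants should watch for. The primary outcome is at 6 months and the cost-utility horizon is one year, so benefit will be reported at time points where nobody was asked the AE question. The trial also measures continued use of the intervention after it has stopped asking about harm.

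Two practical gaps follow. First, an SAE at, say, month 8 falls outside 9.3 but inside a literal reading of 9.4, and two readers could handle it differently. If handling differs by arm (for instance because control participants speak to a therapist), an unblinded comparison would be affected. Second, a TFI alert at month 6 or 12 reaches the participant and the GP but has no stated route to AE or SAE assessment. A SAP cannot repair either gap, because it cannot analyse data that the visit schedule does not collect.

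**Working it through.** The protocol gives no figure for the share of follow-up outside the AE window, so there is none to reproduce.

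**Inputs.** AE window: to month 3, i.e. week 12, with a visit window of 14 days either side (7.10.2). End of follow-up: month 12, i.e. week 52, with 28 days either side (7.10.4). Randomised: 196 in a 1:1 ratio (synopsis), so 98 per arm.

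**Share of follow-up without AE review** = 1 − (AE window ÷ total follow-up).
- In months: 1 − 3/12 = 75.0%.
- In weeks: 1 − 12/52 = 76.9%.
- Smallest share across visit windows (month 3 late, month 12 early): 1 − 14/48 = 70.8%.
- Largest share (month 3 early, month 12 late): 1 − 10/56 = 82.1%.

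**Participant-years, assuming no attrition.** Inside the window: 196 × 0.25 = 49. Outside: 196 × 0.75 = 147 by months, or 196 × 40/52 = 150.8 by weeks.

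**Does the window cover the planned app course?** Baseline may be up to 7 days after randomisation and app access follows at once (7.7, 7.8), so a six-week course ends at about week 1 + 6 = 7. The earliest month 3 contact is week 10. The planned course is therefore inside the window. The same check cannot be made for the control arm, because 8.2 gives neither an end date nor session spacing.

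**Illustration only: bound if an arm of 98 has no events** (one-sided 95%, constant rate, no attrition): −ln(0.05) ÷ participant-years.
- 3 months: 2.996 ÷ (98 × 0.25) = 2.996 ÷ 24.5 = 12.2 per 100 participant-years.
- 12 months: 2.996 ÷ 98 = 3.1 per 100 participant-years.

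**The SAE rule, side by side.** Section 9.3 ends AE collection at month 3. Section 9.4 defines reportable SAEs as a subset of AEs, which implies the same end. The same section also requires all SAEs to be recorded and all study SAEs to be notified, and covers pregnancy at any time in the study, which implies no such end. Both readings are available and the text does not choose.

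**Traffic-light references.** Appendix 3 is the control-arm specification and Appendix 4 is the amendment history. The contents list shows only four appendices, none for this tool.

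**The case against.** The strongest reply is that the 3-month window is deliberate and consistent. Four places state it and the visit lists match. It is about twice the planned app course, and the protocol regards the intervention as low risk (7.4), anticipates no AEs from it (9.3) and knows of no side effects of CBT (9.5). This stands: the AE window is a design choice and the AE passages do not contradict one another.

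A reader might infer that there are no safety data after month 3. The protocol does not support that. TFI, EQ-5D-5L and HUI3, tinnitus-related A&E and healthcare visits, and medication changes are collected at months 6 and 12. TFI alerts and pregnancy reports continue, and withdrawal reasons are documented. Late worsening of tinnitus would be absent from the AE count but present in the randomised TFI comparison. What stops is systematic AE review.

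A reader might also infer that SAE collection stops at month 3. Section 9.4 does not say so; the defect is that 9.3 and 9.4 leave the matter open. Nor is 12 months of access the same as 12 months of exposure, and control therapy lasting that long is possible but not stated.

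Finally, counting every TFI alert as an AE would sit badly with 9.5, which treats fluctuation in tinnitus severity and related mood as expected. It would also recount the primary instrument as a safety endpoint. That objection is right and shapes the fix.

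The medicinal-product phrase looks like template wording: the SAE definition lacks that restriction and 9.2 speaks of the intervention. It is a textual correction, not evidence that AEs would go unrecorded.

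**Conclusion.** The point holds as a gap in systematic AE review and an unreconciled SAE rule. About 75% of planned follow-up time (76.9% by weeks; 70.8% to 82.1% across visit windows) has no planned AE review, and the between-arm AE comparison covers only the first three months. The share rests on nominal visit timing; the participant-year figures also assume no attrition. The zero-event bounds add a constant rate over 12 months, which the protocol does not establish, so they should not be read as the size of the problem.

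The short window is defensible for the expected six-week app course. It is less so for continued app use that the trial itself measures, for control sessions with no stated end, and for focus groups at 6 and 12 months whose related events 9.5 treats as reportable. Sample size, alpha and power are unaffected. This is an inexpensive improvement to safety ascertainment plus a necessary reconciliation of 9.3 with 9.4; the AE definition and the appendix references are secondary.

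**What to change.** 1. Add the existing AE question to the month 6 and month 12 surveys. Amend 9.3, 7.10.3, 7.10.4, Appendix 2, the synopsis and the 4.1 table to match.
2. State one SAE window in both 9.3 and 9.4, running from randomisation to the 12-month contact.
3. Report AEs by arm for 0-3 months, as now specified, and for 0-12 months.
4. State how a TFI alert at month 6 or 12 is assessed for AE or SAE status, consistently with 9.5, without counting every alert as an AE.
5. Reword the AE definition in 9.1 to cover an untoward medical occurrence in a participant of either arm, with no reference to a medicinal product.
6. Correct the traffic-light references in 9.6.1 and include the tool in the appendix cited.

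The cost is two extra items in surveys already being sent, some additional causality review and an amendment. No treatment changes.
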